## Methods and Analysis

### Participants and Recruitment

The present study is a randomized placebo-controlled trial to determine the efficacy of zonisamide for sleep disorders in patients with PD. All procedures were conducted at the Nara Medical University Hospital in Japan. A total of 70 patients were diagnosed with PD according to the International Parkinson and Movement Disorder Society (MDS) diagnostic criteria (28); however, the decline in the striatal uptake on the dopamine transporter in single-photon emission CT does not matter. All patients ≥41 years during the informed consent procurement have at least one sleep problem among the three of the following items: (1) they answered “Sometimes (2–3 times a week),” “Almost none (once a week),” or “Nothing” on item 1 scored regarding “Did you sleep well last week?”; (2) answered “Sometimes (2–3 times a week),” “Many (4–5 times a week),” or “So much (6–7 times a week)” on another item 2 scored regarding “Did you have a bad day at night?” on the PD Sleep Scale (PDSS)-2 Japanese version (29); or (3) they have a score ≥5 on the 10-item no/yes Sleep Behavior Disorder Screening questionnaire Japanese version (RBDSQ) with a maximum score of 13 (30). The PDSS-2 consists of 15 questions regarding PD-related nocturnal symptoms, and it is widely used as a recommended, valid, and highly reliable scale and the validity and reliability of the Japanese version were established (29). RBDSQ provides greater sensitivity and reasonable specificity for RBD compared with polysomnography (31). A cut-off score of ≥5 points has been found to have high sensitivity, specificity, and reliability in the Japanese population (29). All patients have a Mini-Mental State Examination score of ≥22 to preclude the following instructions. All patients are outpatients with Hoehn and Yahr stages 1 to 4 and received oral levodopa before entry. The regimen and dosage of antiparkinsonian medication were stable for at least 2 weeks prior to clinical trial participation.

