### Randomization and Blinding

The patients from the treatment and control groups were randomized in a 1:1 ratio (Figure 1). This study is designed to be single-blind, but the subject allocation was randomized by an independent allocation manager *via* computer-generated block randomization.

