### Primary Outcome

The primary outcome was sleep efficiency (SE), which is the percentage of actual sleep time during sleep (%).

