### Statistical Analysis

The full analysis set (FAS) is defined as the population excluding any of the following: not meeting the eligibility criteria, having received zonisamide within 3 months prior to the trial patient's consent, or having no data after allocation. The per-protocol set is defined as the population excluding participants who violated a protocol from the FAS. The safety analysis set (SAS) is defined as the population receiving zonisamide. The amount of change in SE after the 28-day administration will be compared between the zonisamide treatment group and the placebo group in FAS regarding the primary endpoint. For the secondary endpoint, the change in the ratio of the RWA to total REM sleep epochs, TST, WASO, SOL, the ratio of REM/non-REM sleep, and deep sleep time or alteration of each score of PDSS-2, Pittsburg sleep questionnaire, or RBDSQ will be statistically compared between the treatment group and placebo group in FAS. Adverse event rates are evaluated between the two groups in SAS. The analysis methods include Student's *t*-test, Welch's test (for normally distributed patients with equal or unequal variances, respectively), or Wilcoxon's rank-sum test (for non-normally distributed patients). Statistical significance is defined as a two-sided *p*-value <0.05.

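### The test for the primary endpoint is chosen from the observed data, so whether mean change or rank ordering is tested is not fixed in advance

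*Protocol article*

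**What the plan says.** The Statistical Analysis section of the protocol article sets the primary comparison: "The amount of change in SE after the 28-day administration will be compared between the zonisamide treatment group and the placebo group in FAS". The level is also set: "Statistical significance is defined as a two-sided *p*-value <0.05".

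For the test there is one list, placed after the primary, secondary and adverse-event comparisons and serving all of them. It gives Student's and Welch's tests "for normally distributed patients with equal or unequal variances, respectively", and as the alternative Wilcoxon's "rank-sum test (for non-normally distributed patients"). I read the conditions as referring to the distribution of the outcome.

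No test is tied to SE. The article gives no expected SD or distribution for SE change, so normality and equality of variance can be judged only from the trial's own outcome data.

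**The concern.** The rule does more than choose between two ways of answering one question. Student's and Welch's tests address a difference in mean change. The rank-sum test addresses whether values in one arm tend to exceed those in the other, and it yields no mean difference. The rule therefore lets the outcome data decide which hypothesis the primary p-value refers to.

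Two things are at stake. First, a significant primary result could not be read beforehand as evidence on mean SE change. Second, the nominal 5% level refers to a single test fixed in advance, so one has to ask what the selection step does to it.

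**Working it through.** **Inputs from the protocol article.** Two-sided level 0.05 (Statistical Analysis). Total 70 patients (Participants and Recruitment: "A total of 70 patients were diagnosed with PD"). Allocation 1:1 (Randomization and Blinding), hence 70 / 2 = 35 per arm. The article gives no effect size, SD or power, so it has no figure to reproduce.

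**Assumed, because the article does not give them.** Pre-test rule: Shapiro-Wilk at 5% in each arm; if either is significant, use Wilcoxon; otherwise an F-test at 5%, then Welch if significant and Student if not. The outcome distributions and a dropout case of 30 v 33 are also assumed.

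**Step 1: what each test addresses.**
- Student: (m1 − m0) / [s_p √(1/n1 + 1/n0)].
- Welch: (m1 − m0) / √(s1²/n1 + s0²/n0). With n1 = n0 the two statistics are equal and only the degrees of freedom differ, so the switch that matters is the one to Wilcoxon.
- Wilcoxon: responds to P(X > Y) differing from 1/2.

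Equal means do not imply P(X > Y) = 1/2. Take centred exponential changes with SD 1 in one arm (X) and 1.5 in the other (Y), so both means are 0. Then P(X > Y) = 1 − e^(−1/3) × 1/(1 + 1/1.5) = 1 − 0.717 × 0.6 = 0.570.

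**Step 2: both arms share one distribution (drug has no effect).** With 20,000 trials per scenario, the Monte Carlo standard error is √(0.05 × 0.95 / 20,000) = 0.15 percentage points. Over normal, t3, gamma, lognormal and exponential changes, at 35 v 35 and 30 v 33:
- Assumed rule: 4.8-5.4%. Separate runs gave 5.0-5.3% and 4.5-5.8%.
- Smallest of the three p-values: 6.0-7.0%. Separate runs gave 6.2-6.4% and 5.4-6.8%.
- With truly normal data and equal SDs, about 10% of trials still go to Wilcoxon and about 5% to Welch.

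**Step 3: equal mean change, different spread or shape.** Rejection rates:

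| Assumed changes | Rule | Welch alone |
|---|---|---|
| Normal v gamma (shape 4), equal SD | 6.0-6.2% | 4.8-5.1% |
| Gamma (shape 4), SD ratio 1.5 | 6.7-7.8% | 5.0-5.3% |
| Normal v exponential, equal SD | 8.8% | 5.2-5.3% |
| Gamma (shape 2), SD ratio 1.6 | 11.2-11.6% | 5.2-5.3% |
| Gamma (shape 2), opposite skew | 16.4-16.7% | 5.6-5.8% |
| Exponential, SD ratio 1.5 | 16.2-17.6% | 5.2% |
| Exponential, SD ratio 2 | 26.2-28.8% | 5.4-5.8% |

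Normal changes with SD ratio 1.5 to 2 give only 5.3-5.4% under the rule. Unequal spread is therefore not enough by itself; skew is needed too. Over all the 20,000-trial scenarios, Welch fixed in advance rejects in 4.3-5.8%.

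**Step 4: how skewed is change in SE likely to be?** Beta-distributed SE was simulated with assumed means of 70-85% and SDs of about 12-14 points, 35 per arm, 4,000 trials each. Change had skewness near 0 with one baseline night and −0.12 to −0.38 with the mean of two baseline nights. Wilcoxon was chosen in 10-40% of trials (11-41% in a repeat). The rule rejected in 4.2-5.6%, against 4.0-5.2% for Welch alone.

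**The case against.** The strongest reply is that nothing goes wrong where type I error matters most. Under randomisation against placebo, an inactive drug gives both arms the same distribution of change, and the assumed rule then holds about 5%. The higher rates need a drug that alters spread or shape and leaves the mean unchanged. That is itself a drug effect, and the article never says that means are compared. This stands, and it confines the point to an unfixed hypothesis. The further step, that the 5% level is generally broken, is not supported.

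A reader might also infer that, because SE is a percentage capped at 100, skewed changes are likely and the switch to Wilcoxon will be frequent. The documents do not support this. The endpoint is change, not level, and a difference between two exchangeable capped values is symmetric. Step 4 shows only mild skew and a minority of trials switched. The distributions behind the 11-17% rates are far more skewed (a gamma of shape 2 has skewness 2/√2 = 1.41), and nothing in the article motivates them.

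It is fair, too, that each test is tied to a condition, so the text does not authorise taking the smallest p-value. With no criterion stated, it does not rule that out either.

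Last, a condensed article may leave the pre-test, its threshold and the test for SE to an analysis plan that is not shown. Their absence is no finding. What remains is the rule that is stated: following it, with any threshold, means choosing the test from the outcome data.

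**Conclusion.** The point holds as a defect in a stated rule. The hypothesis behind the sole primary p-value is settled only once the outcome data are seen, and a significant result may not concern mean change in SE. I am confident of this because it follows from the wording alone.

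The consequence for error is conditional. It is near 5% with identical distributions and a mechanical rule, and about 5.5-7% if the smallest p-value were taken. Rates of about 11-17% arise only where markedly skewed changes differ in spread or shape between arms with equal means. Milder cases give 6-9%, and the most extreme one tried gave 26-29%. All these figures rest on assumed pre-tests and distributions. They illustrate what could happen and do not predict this trial.

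This should be changed, because it affects the only primary endpoint and the cure is cheap.

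**What to change.** Name one primary analysis that applies whatever the observed distribution. I would use ANCOVA of post-treatment SE adjusted for the baseline SE already collected, with heteroscedasticity-robust standard errors. Welch's test on change is enough if no adjustment is wanted; naming one test cures the defect, and the adjustment is a further preference. Report the difference in means with its 95% CI. Drop the pre-tests of normality and variance for this endpoint, and keep the rank-sum test as a labelled sensitivity analysis.

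The cost is about one sentence in the protocol or analysis plan, with no new data. The downside is some loss of power if changes prove very heavy-tailed.

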## Discussion

Causal variables for sleep disorders in PD are multifactorial, such as nocturnal motor symptoms, psychosis, depression, and RBD. Sleep parameters obtained from objective gold-standard polysomnography are disturbed in patients with PD rather than in healthy subjects, and these persist during the disease course, and some parameters such as sleep fragmentation, including WASO or RBD, become worse according to the severity of PD (38). Self-report sleep diaries or questionnaires have been widely used in studies, including clinical trials. Each instrument has its own strengths and limitations. The portable EEG/EOG recording system can evaluate natural sleep in the setting of the home, and its advantage of a portable EEG/EOG recording system makes it possible to objectively assess not only conventional sleep parameters but also RBD. The wireless single-channel headband sleep system had moderate-to-high sleep staging agreement between this system and polysomnography in healthy subjects (39); however, there has not been a study validating subjects with the disease. The portable EEG/EOG recording system can objectively diagnose RBD in an outpatient care setting. The present clinical trial evaluated the efficacy of the portable EEG/EOG recording system for the first time.

The mechanism by which zonisamide improves sleep quality is uncertain, but its administration before bedtime might ameliorate nocturnal motor symptoms. Dopaminergic dysfunction may play a role in the pathophysiology of RBD (40). Dopamine modulates the expression of locomotion and other rhythmic motor patterns in central pattern generators (41). The brainstem locomotor pattern generator is responsible for RBD is thought to be modulated by the zonisamide-modified dopaminergic system.

The limitation of this study is the low dose zonisamide administered (25 mg/day). Zonisamide 50 mg/day has revealed a decline in the severity of wearing-off, and its observation can further improve nocturnal motor symptoms.

## Ethics Statement

The studies involving human participants were reviewed and approved by Nara Medical University Certified Review Board (CRB5200002), Japan Registry of Clinical Trials (jRCTs051200160). The patients/participants provided their written informed consent to participate in this study.

